## Abstract

**Background:**

Pancreatic cancer is associated with high mortality and its rates of detection are very low; as such, the disease is typically diagnosed at an advanced stage. A number of risk factors for pancreatic cancer have been reported and may be used to identify individuals at high risk for the development of this disease.

**Objective:**

The aim of this prospective, observational trial is to evaluate a scoring metric for systematic early detection of pancreatic cancer in Mie Prefecture, Japan.

**Methods:**

Eligible patients aged 20 years and older will be referred from participating clinics in the Tsu City area to the Faculty of Medicine, Gastroenterology, and Hepatology at Mie University Graduate School, until September 30, 2022. Participants will undergo a detailed examination for pancreatic cancer. Data collection will include diagnostic and follow-up imaging data and disease staging information.

**Results:**

The study was initiated in September 2020 and aims to recruit at least 150 patients in a 2-year period. Recruitment of patients is currently still underway. Final data analysis is expected to be complete by March 2025.

**Conclusions:**

This study will provide insights into the feasibility of using a scoring system for the early detection of pancreatic cancer, thus potentially improving the survival outcomes of diagnosed patients.

**Trial Registration:**

UMIN-CTR Clinical Trials Registry UMIN000041624; https://tinyurl.com/94tbbn3s

**International Registered Report Identifier (IRRID):**

DERR1-10.2196/26898

## Introduction

Pancreatic cancer is the fourth most common cause of cancer-related death in Japan, and the number of cases is increasing annually [1]. Prognosis for individuals diagnosed with pancreatic cancer is poor, with a 5-year survival rate of 7.9% reported for patients diagnosed between 2006 and 2009 [2]. Pancreatic ductal adenocarcinoma, referred to simply as pancreatic cancer hereafter, is among the most lethal forms of the disease, with an overall 5-year survival rate of approximately 5% [2]. The overwhelming majority of patients with pancreatic cancer present with locally advanced or distant metastatic disease (80%-85%), and only a minority of patients have surgically resectable tumors [3-5]. Following initial evaluation, only 15%-20% of patients undergo resection [6-8]. In many cases, symptoms manifest only when the cancer reaches an advanced stage, such that by the time it is detected, the cancer may be unresectable. Such late detection is among the main reasons for the poor prognosis of patients with pancreatic cancer.

The Japan Pancreatic Cancer Registry has reported 5-year survival rates of 85.8%, 68.7%, and 59.7% for patients with Stage 0, Ia, and Ib disease, respectively [9]. The 5-year survival rate of patients with pancreatic tumors <10 mm (TS1a) approaches 80.4% and that of patients with Union for International Cancer Control (UICC) Stage 0 is 85.8% [6-10]. Therefore, early detection, which enables multidisciplinary treatment including surgical resection, chemotherapy, and radiation therapy, is key to improving prognosis. However, in Japan, the proportion of cases detected at Stage 0, Ia, and Ib is only 1.7%, 4.1%, and 6.3%, respectively [9], indicating that rates of early detection remain low.

Risk factors for pancreatic cancer include family history, diabetes mellitus, chronic pancreatitis, complication of intraductal papillary mucinous neoplasm, smoking, and excessive alcohol intake [11], but an efficient system to detect patients from high-risk groups has not yet been established. A multicenter retrospective study of early stage pancreatic cancer in Japan indicated a role for screening in individuals without symptoms and demonstrated the importance of imaging modalities including computed tomography (CT), active endoscopic ultrasound (EUS), and magnetic resonance imaging (MRI) for identifying abnormalities warranting further investigation [12]. In a previous study, early detection of pancreatic cancer on a regional basis via cooperation between a regional core hospital and the medical association, using EUS and MRI for diagnostic purposes, was effective for detecting Stage 0 pancreatic cancer [13], and another regional study reported the effectiveness of a similar system [14]. Therefore, we aim to implement a system for the early detection of pancreatic cancer in a regional referral setting in Mie Prefecture, Japan.

We hypothesize that referral of subjects for further examinations based on a scoring metric that assesses the presence of known pancreatic cancer risk factors is a feasible strategy to improve rates of early identification of patients with pancreatic cancer compared with current diagnostic practices.

## Methods

### Study Design and Population

This is a prospective, multicenter, observational cohort study for the early detection of pancreatic cancer in Japanese patients. The study was initiated in September 2020 and aims to recruit at least 150 patients. The aim of the study is to assess whether using a scoring metric to screen for known pancreatic cancer risk factors will improve the rate of early identification in this patient population. The flowchart of patient enrolment and evaluation is summarized in Figure 1. The study is registered in UMIN-CTR Clinical Trials Registry (UMIN000041624). Patients who seek consultation at one of five participating local clinics in the Tsu City area until September 30, 2022, will be referred through the regional medical reference system to the Faculty of Medicine, Gastroenterology, and Hepatology at Mie University Graduate School for a detailed examination for pancreatic cancer. 

Prespecified risk factors and associated point scores will be assessed as follows: symptoms (abdominal pain, jaundice, back pain, or weight loss): 1 point; newly diagnosed diabetes mellitus (type 2) or worsening of diabetes: 1 point; family history of pancreatic cancer (parent, child, or siblings, including other types of pancreatic neoplasms): 1 point; abnormal serum amylase level (under 44 U/mL or over 132 U/mL): 1 point; elevated serum CA19-9 level (>37 U/mL [15]): 1 point; pancreatic duct dilation (>3 mm) or pancreatic cyst detected by abdominal ultrasound: 2 points [11]. Adults aged 20 years or older scoring ≥2 points on this metric for prespecified pancreatic cancer risk factors will be eligible for inclusion (those scoring 2 or less but at high risk for pancreatic cancer will be referred for follow-up, but not included in the study). The total number of patients diagnosed with pancreatic cancer and the subsets of patients with surgically resectable pancreatic cancer and Stage 0/I pancreatic cancer will be determined (Figure 1). After registration, participants will undergo hospital visits every 6 months for a period of 2 years.

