### Sample Size

We based our sample size on data from a previous study, in which 28 patients were diagnosed with pancreatic cancer among 224 subjects who had 2 or more pancreatic cancer risks [14]. The risks prespecified in this study are considered equivalent to those reported previously, meaning that the rate of the patients diagnosed with pancreatic cancer is expected to be approximately 10%. To obtain estimation accuracy (95% CI) of ±5%, the required number of subjects is calculated as 138. The planned number of participants in this study is 150. We expect that approximately 100-150 patients with ≥2 points on the pancreatic cancer risk scoring metric will visit the participating clinics per year and that 80% of these eligible patients will give consent to participate in the study [14]. Therefore, in the 2-year referral period, 160-240 participants are expected to enroll in this study. However, when the number of patients reaches 150, registration will continue because this a prospective observational study without any intervention.

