### Statistical Analyses

Patient characteristics will be summarized using descriptive statistics with frequency, mean, and standard deviation. The following items will be evaluated: sex, age, symptoms suggestive of pancreatic cancer (abdominal pain, jaundice, back pain, and weight loss), newly diagnosed or worsening of type 2 diabetes, family history of pancreatic cancer, abnormal laboratory test value for serum amylase (high or low) or serum CA19-9 (high), pancreatic duct dilation, or pancreatic cyst detected by echography. Participants’ BMI and smoking status will also be recorded for use in adjusted analyses.

Loss of participants to follow-up will be minimized by monitoring missed appointments and contacting participants promptly. Where key data items are unavailable or only partially reported, we will use multiple imputation to impute missing data where indicated.

Data on patients with a confirmed diagnosis will be summarized using descriptive statistics according to resectability classification [16]. Binomial logistic regression analysis (both univariate and multivariate analyses) will be performed with a diagnosis of pancreatic cancer as the objective variable and each risk factor and the result of an imaging test as explanatory variables. For the primary multivariable analysis, variables will be selected with a two-sided significance level of 5%. In addition to the unadjusted analyses, logistic regression analyses adjusted for BMI and smoking status will be conducted.

Sensitivity analysis will be conducted to generate multivariable prediction scores based on all available risk factors, regardless of performance or significance on univariable analysis, and based on alternate combinations of risk factors as indicated. Formal comparisons of the relative goodness-of-fit of each model will be conducted through derivation of the Akaike Information Criteria and/or the Bayesian Information Criteria as indicated. We will compare the performance of the prediction score based on this primary model against those of the sensitivity analysis models.

No interim analysis or subgroup analysis will be performed. A separate follow-up study will be conducted to evaluate the 5-year survival rate of pancreatic cancer in the region. SPSS statistical software (Version 25.0, IBM Corp) will be used for all analyses.

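### The amylase limits are printed in U/mL; applied literally, every patient would score the point and the item could not separate normal from abnormal

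*Protocol article*

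**What the plan says.** Under Study Design and Population, the protocol article lists six scored items. The amylase item reads "abnormal serum amylase level (under 44 U/mL or over 132 U/mL): 1 point". The item after it is "elevated serum CA19-9 level (>37 U/mL [15]): 1 point". The entry rule is "Adults aged 20 years or older scoring ≥2 points on this metric for prespecified pancreatic cancer risk factors will be eligible for inclusion".

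Under Statistical Analyses, amylase returns as a patient characteristic, described as "abnormal laboratory test value for serum amylase (high or low", with no limits or unit. The logistic regression takes "each risk factor and the result of an imaging test as explanatory variables".

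Amylase appears in two other places. Follow-Up Assessments lists it among the six-monthly blood tests without a unit. The Discussion reports that, in an earlier regional study, high amylase was more frequent in early pancreatic cancer than in the other groups. Nowhere are the limits restated, given in another unit, or set beside a reference range.

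**The concern.** An item that scores both low and high values as abnormal treats the interval between its limits, here 44 to 132, as the normal band. Some patients must be able to fall inside that band, and some above it. With limits in U/mL this looks impossible, because serum amylase activity in these units is a small fraction of 44.

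The item is an operative part of the instrument that the study sets out to evaluate, so its printed limits matter in three ways:

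- **Entry.** A point that everyone receives lowers the effective threshold for enrolment.
- **Analysis.** An item that takes the same value in everyone has no estimable coefficient in the planned regression.
- **Reuse.** Anyone who takes the score from the article takes the printed limits with it.

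**Working it through.** **1. The plan's own figure.** The Sample Size section expects a diagnosis rate of about 10% and states: "To obtain estimation accuracy (95% CI) of ±5%, the required number of subjects is calculated as 138". The usual precision formula gives

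n = z² × p(1 − p) / d² = 1.96² × 0.10 × 0.90 / 0.05² ≈ 138.3

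This is 138 to the nearest whole number, so the figure reproduces. The amylase item does not enter the formula, so N does not depend on the unit.

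**2. Converting the printed limits.** 1 U/mL = 1,000 U/L, so:

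- 44 U/mL = 44 × 1,000 = 44,000 U/L
- 132 U/mL = 132 × 1,000 = 132,000 U/L

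**3. Applying the printed rule.** The article gives no amylase values. *Assumption:* serum amylase lies between about 20 and 5,000 U/L. The last column shows the result if the same numerals were read per litre. It is there for contrast only.

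| Serum amylase (U/L) | In U/mL | Under 44 U/mL? | Point as printed | Point if 44 and 132 were per litre |
|---|---|---|---|---|
| 20 | 0.02 | yes | 1 | 1 (low) |
| 80 | 0.08 | yes | 1 | 0 |
| 132 | 0.132 | yes | 1 | 0 |
| 300 | 0.3 | yes | 1 | 1 (high) |
| 1,000 | 1.0 | yes | 1 | 1 (high) |
| 5,000 | 5.0 | yes | 1 | 1 (high) |

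A value would have to reach 44,000 U/L to escape the lower limb. That is 44,000 / 5,000 = 8.8 times the top of the assumed range. To count as high it would have to exceed 132,000 U/L, or 132,000 / 5,000 = 26.4 times the top. The result therefore does not depend on where in the range patients fall.

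**4. Effect on entry under the literal rule.** If amylase always gives 1 point, two points need only one more. Patients with the ultrasound finding (2 points) or with two other one-point items qualify anyway. The patients whose eligibility would change have exactly one of the four other one-point items (symptoms, diabetes, family history, CA19-9), no ultrasound finding, and an amylase value inside the band that the item means to treat as normal.

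**5. Effect on the regression under the literal rule.** An amylase variable coded from the printed limits equals 1 for everyone. It is collinear with the intercept and has no estimable coefficient.

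**6. Effect on the expected rate.** The 10% expectation rests on an earlier cohort with at least two risks, in which 28/224 = 12.5% were diagnosed, and on the two sets of risks being equivalent. Admitting patients with only one real risk would weaken that equivalence. The article gives nothing from which to compute by how much.

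**The case against.** The strongest reply is that nobody would apply the rule literally. The item is labelled abnormal, and the analysis section speaks of high or low. A clinician would compare 44 and 132 with the laboratory printout and its flags, whatever unit the protocol prints. On that view the constant item, the lowered threshold and the lost coefficient never occur. This largely stands as a statement about practice: misclassification may be small or nil. It does not make the printed criterion correct, and five clinics score from it.

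A second reply is that the article never states an amylase range, so the error rests on general laboratory knowledge. This is fair, and the range is therefore declared as an assumption. The conclusion holds across all of it. The text also gives some support of its own, since it treats both low and high amylase as findings that can be told apart from normal.

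Three stronger readings are tempting, and the documents support none of them:

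- A reader might infer how far the share of eligible clinic patients would rise. That needs the prevalence of each item among clinic patients and their joint distribution. The article gives neither, nor any count of clinic patients as a denominator.
- A reader might infer that the unit was carried over from the neighbouring CA19-9 item. Two items sharing a unit does not show this.
- A reader might infer that participants have been wrongly enrolled. The full protocol and the scoring sheet are not shown, and nothing indicates what unit the clinics used.

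**Conclusion.** The point holds as a wrong unit, as written, in a threshold that determines score and eligibility. Assuming serum amylase of about 20 to 5,000 U/L (0.02 to 5 U/mL), the printed limits lie far above every value. Literal application would give the point to everyone, the item would not discriminate, and entry would need one further point instead of two in total.

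The effects on entry, on the regression and on comparability with the earlier cohort are all conditional on literal application, for which there is no evidence. The required N of 138 does not change, nor does the definition of the primary endpoint. This is a correction that should be made because the item belongs to the instrument under study. It does not show that the enrolled cohort is compromised.

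**What to change.** 1. Confirm with the laboratory or laboratories the unit in which serum amylase is reported and the range from which 44 and 132 were taken.
2. Reconcile the unit of both limits with that source in the protocol, and in the article by correction.
3. Check that the scoring sheet used by the five clinics carries the same unit.
4. Only if the sheet was applied with the wrong unit, re-check the amylase point, and hence the total score, of participants already scored.

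Steps 1 to 3 cost an enquiry, a one-line amendment and a look at one form. Step 4, if needed, is a check of existing records against the reported amylase values. The sample size and the planned analyses need no change.

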### Study Endpoints

The primary endpoint is the diagnosis rate (number of patients diagnosed/total number of study participants) for pancreatic cancer, calculated with a 95% CI. The secondary endpoints include the diagnosis rates of pancreatic cancer by stage, pancreatic neoplasms other than pancreatic ductal adenocarcinoma, Stage 0/I pancreatic cancer at each visit, and surgical resection. For patients with a definite diagnosis of pancreatic cancer, a frequency table will be created based on the resectability classification [16].

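### High-risk patients with exactly 2 points are both eligible and excluded, because the two halves of the inclusion sentence overlap at that score

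*Protocol article*

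**What the plan says.** The eligibility rule is in Study Design and Population: "Adults aged 20 years or older scoring ≥2 points on this metric for prespecified pancreatic cancer risk factors will be eligible for inclusion". The parenthesis that completes the sentence adds "those scoring 2 or less but at high risk for pancreatic cancer will be referred for follow-up, but not included in the study". The same section sets the points. Five items carry 1 point each (symptoms, diabetes, family history, amylase, CA19-9) and one carries 2: "pancreatic duct dilation (>3 mm) or pancreatic cyst detected by abdominal ultrasound: 2 points".

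The Sample Size section takes its reference rate from an earlier study in which "28 patients were diagnosed with pancreatic cancer among 224 subjects who had 2 or more pancreatic cancer risks", and it counts accrual on the same threshold: "approximately 100-150 patients with ≥2 points on the pancreatic cancer risk scoring metric will visit the participating clinics per year".

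The primary endpoint (Study Endpoints) is the "diagnosis rate (number of patients diagnosed/total number of study participants) for pancreatic cancer, calculated with a 95% CI".

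**The concern.** One sentence gives two rules that cannot both be applied to a high-risk patient with exactly 2 points. Two points is the lowest score that qualifies, and it can be reached in ordinary ways, so the overlap is not a remote case.

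The rule decides who is a study participant, and so who enters both the numerator and the denominator of the primary diagnosis rate. Within score 2, the parenthesis sorts patients by whether they are at high risk of the disease being counted. If it were applied as worded, lower-risk score-2 patients would stay in and higher-risk ones would be left out. The threshold also belongs to the scoring metric that the study sets out to evaluate, so a reader needs to know which population the reported rate describes.

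**Working it through.** **1. The plan's own figures.** Inputs from the Sample Size section: expected rate p = 0.10, 95% CI half-width d = 0.05, 100-150 patients a year with 2 or more points, 80% consent, 2 years.

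- Required number: n = z² p(1 − p)/d² = 1.96² × 0.10 × 0.90/0.05² = 138.29. The stated 138 reproduces.
- Accrual: 100 × 2 × 0.80 = 160 and 150 × 2 × 0.80 = 240. The stated 160-240 reproduces.

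The accrual input is a count of patients with 2 or more points, and the reference cohort had 2 or more risks. Both results therefore belong to a threshold of 2 or more. (The cited 28/224 is 12.5%, whereas the plan uses about 10%. That is a separate matter and does not bear on this point.)

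**2. The two rules side by side.**

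| Score | Judged at high risk? | Main clause | Parenthesis |
|---|---|---|---|
| 0-1 | yes | not eligible | not included |
| 0-1 | no | not eligible | silent |
| 2 | yes | eligible | not included |
| 2 | no | eligible | silent |
| 3 or more | either | eligible | silent |

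The rules conflict in one row only: score 2 and judged at high risk.

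**3. How a score of 2 arises.** Six yes/no items give 2⁶ = 64 patterns. Exactly 2 points comes from the ultrasound item alone (1 pattern) or from any two of the five 1-point items (5 × 4/2 = 10 patterns), 11 patterns in all. This shows that the group is real. It does not show how common it is, because the patterns are not equally likely.

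**4. Direction of the effect under the literal reading.** Let p be the diagnosis rate among all patients with 2 or more points, f the share of them who score 2 and are judged at high risk, and r the diagnosis rate in that share. After they are removed the rate is

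(p − f r)/(1 − f),

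which is below p whenever r exceeds p. Within score 2 alone, removal lowers the rate whenever the judgement of high risk carries any information. The documents give neither f nor r, so the direction is a tendency and the size cannot be computed.

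**The case against.** The strongest reply is that the rest of the article points one way. The main clause sets the threshold at 2 or more, the Sample Size section uses it for both the reference rate and accrual, and no other text shown excludes score 2. The parenthesis then reads most naturally as a slip for patients below the threshold. Figure 1, the enrolment flowchart, is not shown, and neither is the full protocol; either may state the rule correctly and define high risk. Nothing shows that any score-2 patient was turned away, that clinics differed, or even who makes the inclusion decision. Most of this stands, and it limits the severity. It does not remove the contradiction: the article states two incompatible rules, which is different from leaving a detail to a fuller document.

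Two stronger readings are tempting, and the documents do not support them.

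- A reader might infer that the effective threshold is 3 or more, with a large loss of accrual and a higher diagnosis rate. No section states such a rule, and the parenthesis reaches only score-2 patients judged at high risk. Sizing that scenario would need item prevalences and odds ratios that the documents do not give. It would also describe a shift opposite in direction to the one the literal wording tends to produce.
- A reader might infer that the primary endpoint's denominator is itself contradictory. It is not. Study Endpoints defines it clearly as all study participants; what is unclear is whether one subgroup belongs to them.

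**Conclusion.** The sentence is wrong as written. Patients with exactly 2 points who are judged at high risk are both eligible and excluded, and nothing in the text shown settles it. If the parenthesis were followed, the study would select on expected outcome within score 2. The diagnosis rate would tend to fall, provided that the removed patients have a higher rate than the eligible group as a whole. No magnitude can be given.

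On the reading that agrees with the Sample Size section, the parenthesis is a slip and the required 138, the expected 160-240 and the analysis all stay as they are. The correction should be made because the sentence governs who enters the primary estimate. It is a should-fix wording error, not evidence of a faulty design or sample size.

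**What to change.** Reconcile the parenthesis with the inclusion criterion, the Sample Size section and Figure 1, for example by changing it to 'scoring less than 2'. Confirm the single rule to the five clinics. Check the referral and enrolment log for score-2 patients who were not included because of the parenthesis, and report their number with the results, including when it is zero.

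The cost is a short wording correction, one memo to the clinics and one log check. No calculation has to be redone.
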